## Imaging, interventions, follow-up

### First visit

Patients that are eligible for the study will be initially examined and the general medical condition (height, weight, general condition, Karnofsky index, medical history, medication) and the neurological (baseline) status (neurological exam and LENT-SOMA scales) will be assessed. All patients have to be willing and able to undergo repetitive MRI scans. Written informed consent must be obtained at least 24 h prior to surgery and IORT.

### Preceding imaging studies

All patients enrolled will receive preoperative MRI imaging (minimum 1.5 T) including contrast-enhanced T1-weighted magnetization-prepared rapid gradient echo (MP-RAGE) sequences to provide a 3D data set for image-guided surgery. Advanced imaging (such as perfusion or diffusion weighted imaging) may be performed at this stage but is not mandatory.

### IORT planning, risk structures

The optic nerve(s) (or the chiasm, respectively) and the brain stem are defined as risk structures and have to be identified on pre-operative scans. If any risk structure is located ≤2 cm to a T1-enhancing lesion in pre-operative MRIs, intraoperative imaging (e.g. intraoperative ultrasound or in-room CT/MRI) should be used after removal of the tumor (to account for potential brain shifts) to document distances to the applicator surface and to allow dose definition.

### Surgery

The resection procedure should be performed as image-(neuronavigation) guided surgery with techniques that meet individual center standards and preferences. Resection techniques may include suction, bi-/monopolar cautery or ultrasound aspiration. Intraoperative application of 5-aminolevulinic acid (5-ALA) can be used to determine residual tumor tissue. A maximum safe resection approach is recommended, but not mandatory. Due to the possibility of liquor accumulation (or retention) around the applicator and subsequent lowering of doses to the target volume (i.e. the resection cavity wall), ventricular opening during surgery should be avoided whenever possible.

### Frozen section

To establish the diagnosis of GBM, representative tissue samples have to be sent for histopathological examination. The frozen section/cryosection procedure can be performed according to local standards. In case histopathological hallmarks of grade 4 are present, the patient fulfils all inclusion criteria. If the diagnosis of GBM can not be reliably established with cryosection or if additional analyses are necessary, IORT must be omitted.

### Dose prescription and application of IORT

Following establishment of the diagnosis via frozen section and after the surgeon defines the macroscopic (or 5-ALA-delineated) tumor to be satisfactorily removed, IORT will be prepared. All potentially involved risk structures that have been defined in pre-operative imaging (see above) may have displaced consequent to neuro-shifting (i.e. reduced intracerebral pressure and loss of liquor after resection) and should be re-identified with intraoperative imaging (ultrasound or in-room CT/MRI).

For the two risk structures (Optical nerve/chiasm and brain stem), dose constraints of 12 Gy (Optical nerve) and 12.5 Gy (brain stem) are commonly accepted in LINAC-based EBRT according to the QUANTEC (*Quantitative Analyses of Normal Tissue Effects in the Clinic*) recommendations
[26]. Since kV-irradiation shows an increased relative biological effectiveness (RBE)
[27], adapted dose constraints (D_Max_) of 10 Gy apply for both structures during IORT with the (kV-based) INTRABEAM-System. D_Max_ to these structures are then defined intraoperatively on the basis of the dose-depth profiles of the corresponding applicator. If the doses to the risk structures at IORT (D_IORT_) exceed 10 Gy, IORT is technically not feasible and has to be omitted (screening failure). If any risk structure is likely to receive a D_IORT_ of > 10 Gy (e.g., the risk structure has direct contact to the applicator surface) it must be sufficiently shielded with cut-to-size tungsten-filed silicone shielding strips. Shielding with one layer tungsten-silicone strips will reduce the D_IORT_ by 90%.

Based on the cavity geometry and adjacent functional brain areas, the most suitable applicator will be chosen by the team of surgeons and radiation oncologists (sizes rage from 1.5- 5.0 cm in 0.5 cm steps). The applicator will be inserted in the cavity correct positioning and adjacent risk structures will then be again visualized using intraoperative imaging (ultrasound or in-room CT/MRI).

Fluids surrounding the surface should be ruled out or removed. The applicator is then taken out and mounted onto the INTRABEAM system. Next, the arm and the source are covered with the sterile drape and the mounted applicator is again fitted into the resection cavity. Radiation will then be initiated by a radiation oncologist for a defined time span as calculated by the machine software.

After IORT, surgery will be continued in a regular fashion without specific additional requirements.

### Radiation protection issues

IORT has to be delivered in accordance with federal, state and/or local regulations on radiation protection. IORT with the INTRABEAM® System does not require structural alterations if the operating room is approved for C-arm fluoroscopy
[28].

### Early postoperative MRI

Early postoperative MRIs must be performed within a window of 24–48 h after surgery and must be analyzed in a standardized assessment. Before contrast application T1-hyperintense lesions must be used to evaluate residual blood/heme and T2-TSE, T2-FLAIR, and DWI to evaluate ischemia. After contrast application, T1-hyperintense masses or nodules (residual tumor tissue) have to be quantified and the following has to be documented:Complete resection: removal of at least 98% of the T1-enhancing lesions.Subtotal resection: removal of 88-98% of the T1-enhancing lesions.Partial resection: removal of less than 88% of the T1-enhancing lesions.

### Pre-EBRT visit

Before EBRT and concomitant chemotherapy is initiated, all patients will be re-examined (including a neurological exam, an update on medication and a re-assessment based on LENT-SOMA scales) to document changes with regard to the preoperative condition and to exclude contraindications for EBRT (such as impaired wound healing or active infection). Wound healing must be followed with photo documentation.

### External-beam radiotherapy (EBRT) treatment planning

Contrast-enhanced T1- and T2-FLAIR sequences have to be co-registered with the planning CT scan for radiotherapy planning. The planning target volume (PTV) is defined as the peritumoral edema in FLAIR sequences plus a 2 cm margin. Lenses, retinae, optical nerves and/or chiasm and brain stem have to be defined as organs at risk (OAR). The corresponding planning risk volumes (PRV) are defined as OAR plus a 3 mm safety margin. For all OAR, point dose (dose to a volume > 0.03 cm^3^) constraints apply (Table 
1). In case an OAR was pre-irradiated during IORT (with or without shielding), the dose applied to the OAR during IORT (D_IORT_) has to be converted into an dose that is equivalent to a 2 Gy fractionation scheme (EQD2) using an α/β ratio of 2 and considering an RBE of 1.5 as follows (Table 
2 gives exemplary D_IORT_ and EQD2 values):

**Table 1 Tab1:** **Point dose constraints (dose to a volume > 0.03 cm**
^**3**^
**) for OAR**

Risk organ	Maximum point dose (EQD2)
Lenses	7 Gy
Retinae	50 Gy
Optical nerves/chiasm	55 Gy
Brain stem	66 Gy

**Table 2 Tab2:** **Exemplary EQD2 values for various IORT doses (D**
_**IORT**_
**) to risk organs**

D_IORT_	EQD2
3	6 Gy
4	9 Gy
5	13 Gy
6	18 Gy
7	24 Gy

Adequate target volume coverage should be considered by ensuring that 95-107% of the prescribed dose is received by 95% of the PTV. Both, 3D-CRT or IMRT may be applied, beam energies must at least be 6 MV. A total dose of 60 Gy delivered in 30 fractions (2 Gy/fraction) will be applied to the PTV. In case the PTV includes a PRV which would in consequence not receive a dose within the given constraints, a specific risk-organ PTV (PTV-R) has to be delineated to allow separate dose reconstruction.

### EBRT

EBRT must be initiated within 4 weeks after surgery and IORT. All patients will receive five fractions of radiotherapy per week on a conventional linear accelerator (LINAC) with thermoplastic mask fixation. Pausing of radiotherapy is allowed for maximum 5 consecutive days. During EBRT, patients are routinely seen once to twice weekly by physicians and evaluated for adverse reactions.

### Concomitant chemotherapy

During EBRT, all patients will receive concomitant temozolomide-based chemotherapy with a total oral dose of 50 mg/m^2^/d five times per week (on radiotherapy treatment days). Chemotherapy will be initiated at the first day of radiotherapy and will be continued until the last day of radiotherapy. Discontinuation of chemotherapy is allowed for maximum 5 consecutive days.

### Adjuvant chemotherapy

Four weeks after radiochemotherapy, adjuvant chemotherapy with temozolomide is initiated if the patients do not exhibit contraindications (low RBC, WBC and/or platelet counts, previous adverse reactions). The doses will be selected in accordance with the Stupp-protocol (150–200 mg/m^2^/d temozolomide, day 1–5 every 28 days)
[2]. At least six cycles of chemotherapy should be applied. If a patient tolerates the cycling chemotherapy with temozolomide well, additional cycles may be applied.

### Post-EBRT follow-ups

Follow-up visits after radiochemotherapy will be scheduled quarterly. Each visit is preceded by brain MRI imaging studies (contrast-enhanced T1, T2 and T2-FLAIR sequences). Advanced imaging (diffusion- and perfusion-weighted sequences) is optional. The MRI scans are evaluated by a board-certified radiologist or neuroradiologist in accordance to updated RANO criteria (see above). Follow-up visits also include an assessment of the general medical condition (height, weight, general condition, Karnofsky index, medical history, medication) and the neurological status (neurological exam and LENT-SOMA scales).

## Serious adverse events

Treatment-emergent (i.e. IORT-related) events that are fatal, life threatening or classified as LENT-SOMA grade IV toxicity resemble a serious adverse event (SAE) and have to be documented. In case of death an autopsy will be pursued.

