**Methods/Design:**

INTRAGO includes patients aged 50 years or older with a Karnofsky performance status of at least 50% and a histologically confirmed (frozen sections) supratentorial GBM. Safety and tolerability (i.e., the maximum tolerated dose, MTD) will be assessed using a classical 3 + 3 dose-escalation design. Dose-limiting toxicities (DLT) are wound healing deficits or infections requiring surgical intervention, IORT-related cerebral bleeding or ischemia, symptomatic brain necrosis requiring surgical intervention and early termination of external beam radiotherapy (before the envisaged dose of 60 Gy) due to radiotoxicity. Secondary end points are progression-free and overall survival.

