## Methods/Design

INTRAGO resembles a prospective, open-label, single-arm dose-escalation study (Figure 
1). Dose escalation will be conducted in a “classical” 3 + 3 manner with three patients entering each dose level. The decision to escalate to the next dose level is based on safety assessments after all patients of a cohort have reached month 3 (90 days) after IORT: If no dose-limiting toxicities (DLTs) occur in a cohort of 3 patients, the next cohort of 3 patients will be treated at the next higher dose level. If one of the 3 patients in a cohort experiences a DLT, an additional cohort of 3 patients will be treated at the same dose level: If no DLT occurs in the additional cohort, dose escalation will continue at the next higher dose level. Should one or more of the 3 patients in the additional cohort experience a DLT, the MTD is considered exceeded and dose escalation will stop. The preceding dose level will then be considered as the MTD. If two or all of the 3 patients in a cohort experience DLTs, the MTD will be considered exceeded and the preceding dose level will be defined as the MTD. If only a total of 3 patients were treated at the potential MTD level, the potential MTD needs to be confirmed by recruiting an additional cohort of 3 patients: If none or one of the 6 patients experience a DLT, the MTD will be considered confirmed. If two or more patients experience a DLT, the next lower dose level will become the potential MTD. If no DLT occurs at all, the highest dose level will be defined as the MTD. Thus, the MTD is defined as the highest dose at which one or no DLT will have been observed among 6 patients.

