## Management of DLT

Wound infections must be adequately treated, e.g. with dry absorbent dressing and, in case of positive wound swabs, systemic antibiotics should be administered matching to the antibiogram. In all cases of wound infection, blood workup (Complete blood counts, white blood counts, CRP) and imaging studies should be performed (CT or MRI) to rule out intracranial abscesses. Each case of wound infection (our healing difficulty) where conservative therapy fails and surgical revision is required is defined as DLT.

Due to the highly flexible positioning system of the IORT device, cases of cerebral ischemia or bleeding induced by the applicator are unexpected. Nevertheless, both were included into the protocol as DLTs and cases where (venous or arterial) ischemia or intracranial haemorrhage occur as a consequence of the IORT procedure (addition to the baseline risk), adequate therapy is required. Intracranial haemorrhages must be generally surgically removed if mass effects are exceeding the primary lesion volume. There is no symptomatic therapy for arterial or venous ischemia post resection. However, diffusion-weighted imaging (DWI) should be performed to document these events during follow-ups.

If radiation necrosis is suspected in MRI scans and no correlating clinical deterioration is noted, symptomatic therapy may not be necessary and observation is appropriate. For patients with mass effects or neurological symptoms, treatment options include conservative therapy with corticosteroids or anti-angiogenic substances (e.g., bevacizumab) or surgical debulking of the necrotic areas. The decision for either therapy should be made in interdisciplinary consensus (e.g., in interdisciplinary tumor boards). If surgery is required, the corresponding case will be defined as DLT.

All patients will undergo radiochemotherapy and will present five times per week at the linear accelerators. Complete blood counts (CBC), a chemistry panel, liver function tests (LFT) as well as renal function tests (RFT) are regularly performed to screen for hematotoxicity, hepatotoxicity or renal toxicity under temozolomide chemotherapy. Upon intolerance, incompliance or deterioration of CBCs, LFTs or RFTs, the therapy with temozolomide can be discontinued at any time point by any physician in charge. Any discontinuation of chemotherapy for more than 5 consecutive days has to be documented.

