## Discussion

We here present the first dose-finding study on low-energy intraoperative radiotherapy for glioblastoma multiforme. Previous approaches used forward-directed electron beams that only inconsistently provided sufficient target volume coverage, leading to inconsistency in reported outcomes
[15, 29–37]. Within INTRAGO, the spherically irradiating devices of the INTRABEAM system are used to enable geometry-optimized IORT. This may for the first time enable sufficient dose delivery to the resection cavity and to remaining tumor cells.

On may argue that there is no benefit of further dose escalation after resection due to failure of trials involving dose escalation or additional radiosurgery to the tumor bed
[38]. We challenge this conclusion on the basis of two facts that involve the (crucial) time between surgery and adjuvant therapy:

First, it is known that the mean doubling time of a GBM stem cell may be as fast as 24 hours and consequently, the waiting time for EBRT correlates with overall survival
[39, 40]. IORT is embedded in the surgical removal of the mass and thus will likely prevent and/or slow down this exceptionally fast tumor growth in this timeframe. Second, GBM growth shows dose-dependency as early studies showed that doses of at least 50 Gy are required to improve overall survival
[41, 42]. In the RTOG 98–03 trial, patients treated with 66 Gy showed the worst (11.6 months) and those receiving 84 Gy showed the best survival rates (19.3 months) without increased rates of toxicities
[43]. Of note, this study was conducted with rather “old” techniques and in the era of more advanced functional imaging (such as PET) and irradiation techniques (intensity-modulated radiotherapy) dose-escalation may be even more safely and efficiently conducted
[44]. We think that the reason why several other dose-escalation trials were failing is likely to be related to processes occurring during the time between surgery and adjuvant therapy: any wounded site creates a specific stimulatory environment to promote healing, which inadvertently provides remaining cancer cells with strong pro-proliferative, pro-migratory and anti-apoptotic stimuli
[45, 46]. In breast cancer, it has been shown that this unwanted response of the injured microenvironment can be attenuated with IORT

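### Only serious events attributed to IORT must be documented as SAEs, and bleeding or ischaemia is filtered the same way as a DLT, so uncertain attributions pull the safety result low

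*Protocol article*

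**What the plan says.** The section Serious adverse events defines what must be documented: "Treatment-emergent (i.e. IORT-related) events that are fatal, life threatening or classified as LENT-SOMA grade IV toxicity resemble a serious adverse event (SAE". The bracketed gloss makes relatedness to IORT part of the definition of an SAE.

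Among the DLTs, the abstract and the section Assessment of the primary objective (Safety) list "IORT-related cerebral bleeding or ischemia", in the latter as an early DLT within three weeks of IORT. Management of DLT explains the condition: the ischaemia or haemorrhage must "occur as a consequence of the IORT procedure (addition to the baseline risk". The same paragraph says that "cases of cerebral ischemia or bleeding induced by the applicator are unexpected", and then that both were nevertheless included as DLTs.

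The other three DLT types carry no IORT-relatedness condition. Wound problems and symptomatic necrosis count when surgery is required, and early termination of EBRT counts when it is due to radiotoxicity.

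Methods/Design describes a "prospective, open-label, single-arm dose-escalation study". The Discussion notes that "IORT is embedded in the surgical removal of the mass". The dose decision rests on very small counts: "the MTD is defined as the highest dose at which one or no DLT will have been observed among 6 patients".

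**The concern.** Treatment-emergent normally describes timing, and relatedness describes cause. The SAE sentence merges the two, so a causal judgement decides whether an event is documented as an SAE at all, when it should be one item recorded about the event.

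That judgement is weak here. Every patient has a craniotomy in the same session as IORT, so surgery is always a competing explanation for a bleed or an infarct. The treatment and dose level are known to those treating the patient, and there is no control group. An excess over baseline risk is a property of a group. It can seldom be read off a single patient, and the article states neither a baseline rate nor a criterion for attribution.

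Two results are exposed. The SAE table would not show how many serious events followed IORT, so it could not be set against surgical experience. The DLT count, which determines the MTD, would be too low whenever an IORT-caused bleed or infarct is ascribed to surgery. With three to six patients per level, one reclassified event is enough to change a decision.

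**Working it through.** The article gives no baseline rate, expected DLT rate or sample size, so there is no figure of the plan to reproduce. The check applies the protocol's own escalation rule to assumed rates.

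**Rule (Methods/Design).** A level is passed with 0 DLTs in 3 patients, or with 1 in 3 followed by 0 in 3 more. With DLT probability p per patient and independent patients:

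P(pass) = (1−p)³ + 3p(1−p)² × (1−p)³ = (1−p)³ + 3p(1−p)⁵

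- p = 5%: 0.973
- p = 10%: 0.906
- p = 15%: 0.814
- p = 20%: 0.512 + 0.197 = 0.709

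**Can a cohort separate an excess from baseline?** The chance of at least one baseline event in n patients is 1 − (1−b)ⁿ.

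| Assumed baseline b | n = 3 | n = 6 |
|---|---|---|
| 2% | 5.9% | 11.4% |
| 5% | 14.3% | 26.5% |
| 10% | 27.1% | 46.9% |

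The exact 95% interval is 0% to 46% for 0/6 and 0.4% to 64% for 1/6. A bleed unconnected with IORT is therefore plausible at any level, and the cohort data cannot show whether an observed event is excess.

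**What one reclassified event does.** 1/3 against 0/3 decides whether the cohort is expanded. 2/6 against 1/6 decides whether the MTD is exceeded.

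**Effect on passing a level.** Let s be the share of DLTs that are bleeding or ischaemia, and m the fraction of those attributed to surgery although caused by IORT. Taking the DLT types as non-overlapping, the counted rate is p × (1 − s×m). For an assumed true rate of 20%, where P(pass) should be 71%:

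- s = 1/4, m = 1/2: 20% × 0.875 = 17.5%. P(pass) = 0.825³ + 3 × 0.175 × 0.825⁵ = 0.562 + 0.201 = 0.76.
- s = 1/4, m = 1, or s = 1/2, m = 1/2: counted rate 15%, P(pass) = 0.81.
- s = 1/2, m = 1: counted rate 10%, P(pass) = 0.91.

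**Price of the opposite rule.** Suppose every bleed or infarct counted whatever its cause, IORT had no effect, and there were no other DLTs. A level would be wrongly stopped with probability 1 − 0.973 = 2.7% at a 5% baseline and 1 − 0.906 = 9.4% at 10%. The Discussion mentions a dose level III, so there are at least three levels. Over three, the chance of a wrong stop is 1 − 0.973³ ≈ 8% and 1 − 0.906³ ≈ 26%.

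**The case against.** **Excluded events are not lost.** A reader might infer that they cannot be examined later. The documents do not support that. An MRI at 24–48 hours assesses blood and ischaemia in every patient, repeated clinical and LENT-SOMA examinations are planned, death from any cause enters overall survival, and an autopsy is pursued in case of death. This stands: the events leave the SAE and DLT counts, not all records. The repair is only partial, though. The early scan covers two days of a three-week DLT window, and none of these records is tied to the DLT or SAE result.

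**No default attribution to surgery is stated.** A reader might infer one from the remark that applicator-induced events are unexpected. That remark concerns injury by the applicator, and the next sentence keeps both events as DLTs. A direct applicator injury may also be recognisable. The supportable claim is that attribution is uncertain, not that it is impossible or decided in advance.

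**The baseline-risk condition is not general.** It is written for bleeding and ischaemia only; the SAE section says just IORT-related. The filter also touches one of four DLT types, so a rise in P(pass) from 71% to 91% is an extreme case and not a typical one.

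**Conditioning a DLT on relatedness is defensible.** The objective is the MTD of IORT, and counting surgical events would push it down. The DLT list sets no severity threshold for bleeding or ischaemia, so counting all such events by default could also bring in minor imaging findings. Together with the wrong-stop probabilities above, this is a good reason to leave the DLT definition as it is. It is no reason to leave unrelated serious events undocumented as SAEs.

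**Conclusion.** The point holds for the SAE rule as written. Under it, a fatal, life-threatening or LENT-SOMA grade IV event judged unrelated to IORT is not an SAE, so the SAE count can only equal or fall below the number of such events that occurred. This follows from the wording and needs no assumed rate.

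For the DLT, the point is narrower. The IORT-related condition is a legitimate choice, but it rests on an individual attribution that this design cannot make reliably, and nothing shows how far the MTD depends on it. The count is too low to the extent that IORT-caused bleeding or ischaemia is ascribed to surgery; a surgical event ascribed to IORT would err the other way.

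At an assumed true DLT rate of 20%, P(level passed) moves from 71% to about 76% with a quarter share and half attributed away. It reaches 91% only if half of all DLTs are lost. Share, misattribution fraction and true rate are all assumptions, because the article gives none of them.

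**What to change.** - **Serious adverse events:** remove the gloss that equates treatment-emergent with IORT-related. Require documentation of every fatal, life-threatening or LENT-SOMA grade IV event after IORT regardless of cause, with relatedness to IORT as a separate field.
- **Assessment of the primary objective (Safety) and Management of DLT:** keep the IORT-related DLT. Add that every postoperative bleeding or ischaemic event is recorded and reported with its attribution and the reason for it, whether or not it was counted.
- **Analysis of the MTD:** add a sensitivity analysis showing, level by level, whether the decision would change if the uncounted bleeding and ischaemic events were counted as DLTs.

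The cost is an amendment of wording, a few more SAE forms and one short listing. The escalation rule, the DLT definition and patient care do not change, so the wrong stops calculated above are not incurred.
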